## Methods

### Study Design

On the basis of our primary study outcome (feasibility), we will conduct a 2-phase single-arm study [42,43] to preliminarily test our mHealth-based fiber intervention in up to 80 young adults with prediabetes (phase 1) and elucidate factors that impact sustained behavior change and fiber intake after intervention end using EMAs (phase 2) (Figure 1).

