### Data Collection

#### Phase 1

Participants will complete 2 in-person data collection sessions at the University of Oklahoma Health Campus in Tulsa, one at baseline and one after the 3-month intervention (postintervention time point). Each time, they will be asked to fast for 10 hours and have a venous blood draw done, complete anthropometric assessments, and complete a measure of capillary fasting blood glucose. Venous blood samples will be collected and processed for assessment of fasting insulin. Fasting capillary blood glucose and venous insulin will be combined to calculate the Homeostatic Model Assessment of Insulin Resistance (HOMA-IR) using established calculations (fasting glucose in mmol/L × fasting insulin in μU/mL/22.5) [53,54]. If no HbA_1c_ value is on file for the previous 3 months, HbA_1c_ will be checked using an A1CNow Self Check system (PTS Diagnostics), which will be rechecked at the postintervention time point. On 2 random days after completing the baseline visit, participants will also complete 2 separate Automated Self-Administered 24-hour dietary recalls (ASA-24) to quantify fiber intake. They will also complete surveys, including a measure of basic demographic variables. Surveys will be administered in REDCap [55,56].

During the intervention period, participants will complete daily EMAs on the Insight mHealth app maintained by the University of Oklahoma Health Campus OU Health Stephenson Cancer Center mHealth Shared Resource. This will include a run-in period, where the Insight app will deliver a morning daily diary, a midmorning diary, and a midday diary. This will decrease to only a morning daily diary during the intervention period. The morning daily diary is delivered 30 minutes after waking, before typical morning mealtimes. The midmorning and midday EMAs will be delivered approximately 2 hours after normal first and second mealtimes for the day. The morning daily diary will include a checklist-type assessment of intake of high-fiber foods and static measures such as sleep, whereas all daily diaries will assess affect, food cravings, digestive symptoms, feelings of “lack of time,” motivation to eat high-fiber foods, and urge to eat tasty food. Participants will also be presented with participant-initiated questions on the app to report when a study-provided food was eaten.

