### Statistical Analysis

#### Power

The focus of this project is to test feasibility; thus, for phase 1, we will recruit based on existing recommendations for feasibility studies (ie, N≥30) [58]. However, we will maximize sample size for robust EMA data in phase 2. Specifically, for phase 2, the purpose is to examine factors that influence sustained intervention effects. We anticipate that all individuals who complete postintervention data collection (n=64; 32 each year, 80% retention) will begin EMAs. Per past EMA studies, we estimate 75% compliance with EMAs. For questions only asked in the morning daily diary (eg, sleep), each participant will complete approximately 21 daily diary responses (1 per day × 28 days × 0.75 compliance). Thus, with an effective sample size of 237 based on a conservatively high estimate of the correlation between daily assessment of sleep (0.7 × 1344 EMA responses), we will have 80% power to detect an association of a relatively small effect size (Cohen *f*^2^=0.034) between sleep and fiber intake. When examining associations between fiber intake and momentary predictors, which are assessed multiple times per day (eg, stress), we will be able to detect even smaller effect sizes.

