#### Analytic Plan

For phase 1, we will compute descriptive statistics (for all feasibility metrics) and 2-tailed paired *t* tests to examine changes in our preliminary efficacy outcomes (fiber intake, HbA_1c_, and HOMA-IR) from baseline to the postintervention time point as a measure of preliminary efficacy. For phase 2, the primary goal is to determine whether participants maintain fiber intake after the intervention and identify real-time factors that predict adherence. Adherence will be defined as maintaining fiber intake at or above 80% [59] of postintervention levels based on ASA-24 data at the start and end of the 4-week EMA period. A logistic multilevel model will be used to predict adherence (1=maintained; 0=dropped below threshold) from EMA-measured factors (eg, affect). EMA predictors will be aggregated at the participant level (eg, mean stress across the EMA period) to assess overall exposure to these factors, whereas daily fluctuations will be modeled using within-person deviations from each participant’s mean. To assess how the influence of these predictors changes over time, we will use time-varying effect modeling, allowing for the examination of whether certain factors (eg, stress) exert stronger effects on adherence early vs late in the observation period. Additionally, we will explore the role of EMA variability, calculating within-person fluctuations (eg, SD of stress) to test whether greater instability in these factors predicts lower adherence. We will assess patterns of missing data and conduct sensitivity analyses assuming different missing data mechanisms. For example, we will consider a multiple imputation approach, which uses baseline characteristics to account for potential missing at random mechanisms [60,61].

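### If the seven or more EMA items enter the phase 2 adherence model together by ordinary maximum likelihood, about 64 outcomes (at most 32 in the rarer class) would inflate real associations by roughly 20% to 30%

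*Protocol article*

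**What the plan says.** The Analytic Plan defines adherence as keeping fiber intake at or above 80% of the postintervention level, judged from ASA-24 recalls at the start and end of the four-week observation period. The Data Collection section (Phase 2) places the closing recalls once, after that period. Each participant therefore has one adherence status.

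The model is given in the singular and its predictors in the plural: "A logistic multilevel model will be used to predict adherence (1=maintained; 0=dropped below threshold) from EMA-measured factors (eg, affect"). Predictors enter as person means, with daily fluctuations as deviations from those means. In a separate sentence the plan adds an exploration of within-person SDs, "to test whether greater instability in these factors predicts lower adherence".

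On the items, the Data Collection section (Phase 1) says that "all daily diaries will assess affect, food cravings, digestive symptoms" and three more: lack of time, motivation and urge to eat tasty food. Sleep is asked in the morning diary. Phase 2 uses the same variables. That makes at least seven items. The Power and Analytic Plan sections also name stress.

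The Power section expects "n=64; 32 each year, 80% retention" to start phase 2. Its only power figure for phase 2 concerns the association of sleep with fiber intake, "with an effective sample size of 237 based on a conservatively high estimate of the correlation between daily assessment of sleep (0.7 × 1344 EMA responses").

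**The concern.** In a logistic model the information is limited by the smaller outcome group, not by the number of rows. With few outcomes per coefficient, unpenalised maximum likelihood pushes real effects away from zero. This bias arises even when the model is correct, and it is distinct from multiplicity.

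Identifying factors that predict adherence is part of the stated primary goal of phase 2. If several items are fitted jointly, the odds ratios of the factors that do matter would tend to look larger than they are, and follow-on intervention targets could be chosen on those sizes. The large diary count in the Power section may also suggest more information than the adherence model has.

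**Working it through.** **Inputs from the article.** Enrolment of up to 80 (Study Design); 80% retention and 75% EMA compliance over 28 days (Power); six items in every diary plus sleep (Data Collection); one binary status per person (Analytic Plan).

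**The plan's own figures.**
- Participants entering phase 2: 80 × 0.80 = 64.
- Diary responses: 64 × 28 × 0.75 = 1344.
- Effective sample size: 237 is reproduced by n(1 − r)/(1 + r) = 1344 × 0.3/1.7 = 237.2.
- Power with one predictor, N = 237, f² = 0.034 and an assumed two-sided alpha of 0.05: 80.7%, in line with the stated 80%.

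These figures hold for a linear association of sleep with fiber intake. They do not describe a binary outcome in 64 people.

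**Why the diaries do not help.** Adherence is constant within a person, so a participant's deviations from their own mean cannot explain it. The 1344 responses measure the predictors more precisely but add no adherence outcomes.

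**Outcomes per coefficient.** The rarer class of 64 people is at most 32, whatever the drop rate. With seven person means, 32/7 = 4.6. With stress as an eighth item, 32/8 = 4.0. The article gives no drop rate. If 20% to 40% drop (an assumption), there are 64 × 0.20 = 12.8 to 64 × 0.40 = 25.6 drops, or about 13 to 26. That gives 13/7 = 1.9 to 26/7 = 3.7 per coefficient.

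**Size of the bias.** Monte Carlo, 1500 runs per setting: n = 64, person-level unpenalised logistic regression, normal predictors correlated 0.3, one true slope of 0.70 per SD. Inflation is the mean estimate divided by 0.70, minus 1.

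| Expected drops | Outcomes per coefficient, 7 terms | Mean estimate, 7 terms | Inflation | Mean estimate, 1 term | Inflation |
|---|---|---|---|---|---|
| 13 | 1.9 | 0.915 | 31% | 0.743 | 6% |
| 19 | 2.7 | 0.856 | 22% | 0.759 | 8% |
| 26 | 3.7 | 0.842 | 20% | 0.753 | 8% |
| 32 | 4.6 | 0.839 | 20% | 0.753 | 8% |

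Across repeat simulations the seven-term mean estimate ranged from about 0.83 to 0.92, and one-item models inflated by about 4% to 8%. As odds ratios per SD, exp(0.70) = 2.01 becomes exp(0.83) = 2.29 to exp(0.92) = 2.51. Firth-penalised fits of the seven-term model gave about 0.68 to 0.75 across the simulations.

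**If the SDs were put into the same model.** With 14 terms there are at most 32/14 = 2.3 outcomes per coefficient. The mean estimate is then 1.02 (32 drops) to 1.25 (13 drops), which is 46% to 79% too large. The plan does not describe this model.

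**The case against.** The strongest reply is that the article does not commit to the fit that causes the bias. It does not say that the items enter together, nor that estimation is unpenalised. Both may be settled in an analysis plan that is not shown, and their absence from a condensed article is no defect. If items are fitted one at a time, the inflation is about 4% to 8% and hardly matters. This stands, and it is why the point is conditional. What remains is that the article itself fixes the outcome, the model class, the predictors and the sample size, and that one model with several factors reads most naturally as joint.

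Four stronger readings are tempting, and the documents do not support them.

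- **About 14 terms in one model.** The SDs are introduced as a further exploration. Entering them alongside the means is an inference.
- **Only 13 to 26 drops.** This rests on an assumed 20% to 40% rate. What follows from the article is a ceiling of 32.
- **Apparent prediction where none exists.** With seven predictors and no true effect, mean coefficients were 0.00 to 0.01 and each term was rejected in 4.9% to 5.7% of runs, so irrelevant factors are not biased. The chance of at least one significant term, 1 − 0.95^7 = 30% for independent tests, is multiplicity. The apparent AUC does average 0.68 to 0.73 under the null with seven terms, but the article plans no AUC.
- **Estimates too large on balance.** Adherence is a cut on fiber intake from a few 24-hour recalls, and misclassification pulls slopes toward zero. With an assumed 15% misclassified, the seven-term mean estimate was 0.44 to 0.56, below 0.70. Without misclassification the bias of 0.12 to 0.19 compares with a standard error of 0.38 to 0.51.

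**Conclusion.** The point holds in a limited form. On the natural joint reading, the adherence model has at most 4.6 outcomes per coefficient, and ordinary maximum likelihood would overstate a real association of 0.70 per SD by roughly 20% to 30%. A floor of about 20% remains at the most favourable 32:32 split, so the conclusion does not depend on the assumed drop rate.

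It does depend on joint entry of seven person means, unpenalised fitting, predictors correlated about 0.3 and a correctly classified outcome. The net direction of error in the real data is not established. The severity is minor: the primary outcome is feasibility, the bias is smaller than the standard error, and the Limitations section already leaves firm effect claims to later randomised trials.

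**What to change.** In the Analytic Plan:

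1. Fit the adherence model at the person level, one row per participant, with Firth-penalised logistic regression.
2. State that the information for this model is about 64 adherence outcomes with at most 32 in the rarer class, and that the effective sample size of 237 in the Power section does not apply to it.
3. Label any model that enters several EMA items together as exploratory. If a discrimination measure is reported, give the optimism-corrected value.

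Making one item per model the main result is an option, not a requirement: it limits the inflation but gives up mutual adjustment.

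The cost is a few sentences and standard software, with no new data. The downside is slight shrinkage of the estimates. The article, as of March 2026, slated enrolment to begin in April 2026, so at that date the wording could still be settled before any outcome data existed.

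### The imputation suggested as a phase 2 sensitivity analysis names only baseline characteristics as inputs; it should also hold the fiber outcome and the EMA predictors of the model it checks

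*Protocol article*

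**What the plan says.** The relevant text is in the Protocol article, Statistical Analysis, Analytic Plan.

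- **Missing data.** "We will assess patterns of missing data and conduct sensitivity analyses assuming different missing data mechanisms". As an example, the team would consider multiple imputation, "which uses baseline characteristics to account for potential missing at random mechanisms". The text does not say which variables would be imputed, and baseline characteristics are the only inputs named.
- **Phase 2 outcome.** "Adherence will be defined as maintaining fiber intake at or above 80% [59] of postintervention levels based on ASA-24 data", taken at the start and end of the 4-week EMA period. Postintervention fiber is therefore the denominator of the outcome.
- **Phase 2 model.** A logistic multilevel model relates adherence to EMA factors. These enter as person means and within-person deviations and, in a further exploratory step, as within-person SDs. No imputation is stated for this model.
- **Size and expected missingness (Power).** Phase 2 starts with "n=64; 32 each year, 80% retention", and "we estimate 75% compliance with EMAs". No missing share is given for the recalls at the end of observation.

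**The concern.** An imputation model should contain at least the variables of the analysis it serves. Here the reference fiber value and all phase 2 EMA predictors are measured after baseline. If a missing end-of-observation outcome is drawn from baseline data only, the drawn values relate to the EMA factors only as far as baseline explains both. Mixing such values with the observed ones dilutes the association under study.

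The sensitivity analysis would then show a weaker association because of how it was built, not because of the missing data. A reader comparing it with the main result could wrongly conclude that the main result is fragile.

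Some missing end recalls are plausible. They are unannounced and come after four weeks of EMA, and the payments listed under Ethical Considerations (screening, follow-up visit, EMAs) include none tied to them.

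**Working it through.** **1. The plan's own phase 2 figure.** Retained participants: 80 × 0.80 = 64. Diary responses: 28 × 0.75 = 21 each, and 64 × 21 = 1344. With a first-order autocorrelation of 0.7, the effective sample size is 1344 × (1 − 0.7)/(1 + 0.7) = 237.2, against 237 stated. With one predictor and a two-sided alpha of 0.05 (assumed), f² = 0.034 gives 80.7% power, against 80% stated. The figure reproduces but says nothing about imputation, so the effect of imputation has to be simulated.

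**2. Inputs.** From the document: 64 participants, 28 days, 75% EMA compliance (so 25% of prompts missing), adherence as a binary outcome, and EMA person means as predictors. Assumed: true log odds ratio β of 0.5 to 1.0 per SD, baseline–predictor correlation of 0.3, 10% to 30% of outcomes missing, and an intraclass correlation (ICC) of 0.3 to 0.7 for prompts. A person-level logistic model stands in for the multilevel model.

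**3. Whole outcome missing.** Baseline B is standard normal; X = 0.3B + √0.91 × noise; logit P(Y = 1) = βX + 0.3B. The outcome is missing at random given B: logit P(missing) = log(m/(1 − m)) + 0.3B. The simulation used 40,000 people and 10 imputations, and the analysis regressed Y on X and B. Coefficients of X at β = 0.7:

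| Missing | Full data | Complete cases | Imputed from B only | Imputed from B and X |
|---|---|---|---|---|
| 10% | 0.709 | 0.708 | 0.628 | 0.708 |
| 20% | 0.697 | 0.694 | 0.531 | 0.690 |
| 30% | 0.693 | 0.698 | 0.461 | 0.697 |

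Share retained with B only: 0.628/0.709 = 0.89; 0.531/0.697 = 0.76; 0.461/0.693 = 0.67. This is slightly below 1 − m (0.90, 0.80, 0.70), the value expected if the imputed share carried no association at all.

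Across β = 0.5 to 1.0, and also when a whole person-level predictor is imputed instead, the extremes were:

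- 0.520 to 0.467, a loss of 10% (β = 0.5, 10% missing).
- 1.006 to 0.645, a loss of 36% (β = 1.0, 30% missing, predictor imputed).

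Adding the other analysis variable restored the full-data value within about 1% throughout. A separate simulation with a steeper slope (about −1.08 per SD) agreed: 86%, 74% and 62% were retained at 10%, 20% and 30% missing. About 100% was retained once postintervention fiber and the EMA mean were added together.

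**4. Scattered prompts missing.** Here x = u + e over 28 occasions, with 25% missing at random and imputed from B without a person effect (20,000 people, 5 imputations).

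| ICC | Person-mean coefficient per unit, full → imputed | Per SD, full → imputed | Within-person SD, full → imputed |
|---|---|---|---|
| 0.3 | 1.167 → 1.424 (+22%) | 0.665 → 0.654 | 0.828 → 0.895 (+8%) |
| 0.5 | 0.965 → 1.213 (+26%) | 0.697 → 0.697 | 0.700 → 0.823 (+18%) |
| 0.7 | 0.793 → 1.023 (+29%) | 0.666 → 0.678 | 0.542 → 0.742 (+37%) |

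The reason is that filled-in prompts pull each person's mean toward the baseline prediction. The means then spread less, and one unit stands for more. Simply averaging the available prompts gave 1.134, 0.952 and 0.789, within 3% of full data.

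**The case against.** The strongest reply is that the article commits to no such model. It says that imputation uses baseline characteristics, not that it uses nothing else, and it excludes no variable. Baseline data could be meant as auxiliary variables added to those of the analysis. The sentence is an example of something to be considered, within sensitivity analyses. A full list of imputation variables commonly sits in an analysis plan, which is not shown here. The missing shares and effect sizes above are also assumed.

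Most of this stands, and it limits the point. Four stronger readings are tempting, and the document supports none of them:

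- *Imputation will rest on baseline data and nothing else.* That is one reading of the sentence, not its wording.
- *The main phase 2 associations are biased.* No imputation is stated for the main model, and no rule lets one sensitivity analysis override it.
- *The bias always runs toward zero.* Step 4 shows the opposite on the per-unit scale for scattered prompts, which are the only phase 2 EMA missingness the article quantifies.
- *Leaving out postintervention fiber causes the shrinkage.* No simulation isolates this. By reasoning, the omission loses information on the outcome's denominator and makes missing at random less credible.

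One thing survives. The sentence goes beyond silence: it ties the missing-at-random assumption to baseline data. An analysis plan that carried it over as written would inherit the problem. If missingness does depend only on baseline, complete cases in step 3 were already within about 1% of full data, so baseline-only imputation would be worse than the analysis it checks.

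**Conclusion.** The point holds in conditional form and at low severity. If adherence or end fiber is imputed without the EMA predictors, the imputation model is incompatible with the phase 2 analysis. The sensitivity estimates then shrink by about 10% to 36% for 10% to 30% missing outcomes. If scattered prompts are imputed from baseline only, person-mean coefficients per unit rise by 22% to 29% at 25% missing, per-SD coefficients hardly change, and within-person SDs are inflated by 8% to 37%. Those SDs are themselves planned predictors; the effect on their coefficients was not simulated.

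These sizes rest on the assumptions in step 2 and on a simplified person-level model. They show the mechanism and do not forecast this trial's result.

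**What to change.** Replace the clause on baseline characteristics with a statement along these lines:

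> Any imputation model will include, besides baseline characteristics, postintervention ASA-24 fiber, end-of-observation ASA-24 fiber and the EMA predictors of the analysis model being fitted. End fiber will be imputed as a continuous value and adherence derived from it afterwards. Where EMA prompts are imputed, the model will account for clustering within persons.

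Keep the model small. The article names about eight EMA factors (affect, cravings, digestive symptoms, lack of time, motivation, urge to eat tasty food, sleep, stress). Their means and SDs, with two fiber values, the food checklist, EMA completion and content views, make 8 × 2 + 5 = 21 variables for about 64 people, roughly three people per variable. A model of that size has not been tested. So build one imputation model per analysis model, and add auxiliary variables such as the fiber checklist or EMA completion only as far as the sample allows.

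The cost is one sentence and slightly more programming. No new data are needed, and the article places the start of enrollment in April 2026, so the wording can be settled before outcomes are seen.

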## Results

This study was funded and initiated in July 2025. As of March 2026, the mHealth intervention content is being built, with completion of app development and trial enrollment slated to begin in April 2026.

## Discussion

### Expected Findings

This protocol describes a first-of-its-kind examination of a fully remote mHealth intervention that focuses singularly on promoting intake of fiber in young adults with prediabetes. This protocol and resulting data will shed light on two key factors: (1) the utility of an mHealth intervention in young adults and (2) the potential effects of a singular focus on fiber in prediabetes.

Diet is a central mechanism driving increased incidence of diabetes in young adults and current trends in rates of prediabetes [1,2,33]. Questions remain on the ideal diet targets to improve glycemic control and lower risk. Historically, a key focus has been on promoting a negative energy balance to facilitate weight loss, an approach that is efficacious compared to standard-of-care pharmaceutical intervention [62]. However, as in other chronic diseases, maintaining this negative energy balance is challenging. Therefore, there is interest in alternative approaches that are simple to conceptualize yet effective for improving glycemic control. From this perspective, decreasing total carbohydrates as in a ketogenic or carnivore diet is highly appealing. Carbohydrates are the nutrient responsible for increases in blood glucose; thus, their elimination would result in a decreased frequency of blood glucose spikes. Decreasing carbohydrates in this manner may also result in weight loss as individuals do succeed in losing weight on carbohydrate-restricted diets [63]. However, this may only mask underlying insulin resistance if fiber in the diet is key to improving glucose regulation. Indeed, recent evidence highlights the potential of fiber to facilitate microbiome modulation, resulting in improved glycemic control and response to pharmaceutical intervention [64]. However, this may only occur with foods high in intrinsic fiber, not isolated or synthetic fiber supplementation (eg, isolated psyllium husk) [65].

While fiber can be consumed in the context of low-carbohydrate diets, options that are both low in carbohydrate and high in intrinsic fiber are few. Furthermore, carbohydrate-containing fiber sources may be germane for reducing diabetes risk. In the empirical diabetes risk reduction diet, nuts (hazard ratio [HR] 0.57 for White adults and 0.65 for adults from minority groups) and cereal fiber (HR 0.9 for White adults and 0.95 for adults from minority groups) are both associated with reduced diabetes risk [12]. This is contrasted with red and processed meat, which has an HR of 1.34 for White adults and 1.14 for adults from minority groups [12]. Nuts are indeed low in carbohydrates, with 1.9 g of carbohydrates for every 1 g of fiber (ie, a 1.9:1 carbohydrate-to-fiber ratio) [66]. Some cereals, such as oats, have a higher carbohydrate content but still a relatively low carbohydrate-to-fiber ratio (6.7:1). Existing research shows that greater reliance on foods with less than a 10:1 ratio is associated with lower fasting glucose and HOMA-IR [66].

Cereal fiber can be consumed in isolated or synthetic forms present in specialty food products that may or may not have lower total carbohydrate content. Whether these have the same effects as intrinsic cereal fiber is not well known, and effects may be limited to cholesterol [67]. If the other food components present in intrinsic fiber sources (eg, polyphenols) are partially responsible for the protective glycemic effects, specialty food products may not prove advantageous. In their recent systematic review and meta-analysis, Colak et al [68] concluded that whole foods—as compared to supplemental sources—only improve HbA_1c_ versus other measures of glycemic control. However, most whole food–based studies included in their review appeared to be whole food sources of isolated or synthetic fibers (eg, “soy fiber in cookies”) vs food sources of intrinsic fiber (eg, soybeans). This is a vital distinction given the influx of products on the market that are markedly high in isolated or synthetic fiber.

Despite the potential benefits of eating more whole fiber, individuals may be reluctant to do so given that fiber is itself a carbohydrate and commonly coexists with digestible carbohydrates such as starch [30]. For example, per 1-cup serving, white beans contain 42.6 g of digestible carbohydrates and 13 g of fiber, whereas a food such as green beans has 4.8 g of digestible carbohydrates but only 3.5 g of fiber. Thus, if it is fiber intake—vs carbohydrates per se—that lowers risk of diabetes, a slightly higher carbohydrate intake to enable sufficient fiber may be necessary [69]. This is particularly true as fiber intake in excess of 30 g per day is associated with the greatest reduction in risk. In their systematic review and meta-analysis, Reynolds et al [69] observed a dose-response relationship between fiber intake and type 2 diabetes risk, including up to 45 g per day. Ingesting sufficient fiber via low–fiber density foods (such as green beans or nuts) may result in excessive calorie or total food intake, and fiber-dense sources (such as legumes) may be essential. The use of CGMs, as in this study, may help individuals observe the differences between acute increases in blood glucose and improved insulin sensitivity, key distinctions when adding fiber-containing foods to the diet. While the starch in foods such as beans may cause acute increases in glucose, this alone is not indicative of insulin resistance. Continuing to rely on foods such as these may improve long-term glucose regulation despite short-term increases in serum glucose levels [70].

Promoting greater intake of intrinsic fiber sources can also serve as an approach to behavior change. As outlined in the study by Ma et al [5] and others [8], by promoting greater intake of foods high in intrinsic fiber, participants are in essence merely working toward adoption of an overall healthy dietary pattern (eg, increasing intake of fruits, vegetables, whole grains, and beans or legumes) but via a singular focus on foods high in fiber. Existing data show that conventional advice to eat more plants, fruits, and vegetables or promote adoption of other disease-protective dietary patterns (eg, the Mediterranean diet) does not necessarily translate into improvements in fiber intake sufficient to meet levels that are associated with the highest disease risk reduction [71,72]. However, there is emerging evidence suggesting that greater fiber intake may be associated with greater improvements in multiple effects, such as sleep and mood, which may offer a greater return on investment, promoting and incentivizing long-term maintenance [73-75]. If intervention guidance is relatively simple and offers greater potential for perceived physiological change, it may promote intake in the long term.

